#### **6.1.2 Secondary outcome measures**

1. Difference in mean systolic blood pressure, in mmHg at 6 and 24 months of follow-up between intervention and control groups determined at physicians' practice with a validated automatic electronic sphygmomanometer.
2. Difference in mean diastolic blood pressure, in mmHg at 6, 12 and 24 months of follow-up between intervention and control groups determined at physicians' practice with a validated automatic electronic sphygmomanometer.
3. Percentage of patients with SBP <140 mmHg and DBP <90 mmHg at 6, 12 and 24 months of follow-up.

4. Quality of life (as measured by EuroQoL-5D) at 6, 12 and 24 months of follow-up.
5. Adherence measured by proportion of days covered (PDC) at 6 and 12 months of follow-up.
6. Persistence, defined as period of continuous use of the corresponding drug from the beginning of the follow-up until its discontinuation at 6 and 12 months of follow-up.
7. Therapeutic inertia (TI), defined as the number of patients whose pharmacological treatment had not been modified, divided by the number of patients not reaching the target values (SBP and/or DBP measurements taken at 6 and 12 months of follow-up), according to the recommendations of the European Society of Hypertension and European Society of Cardiology (19).

Other outcome measures:

1. Changes in lifestyle (smoking, exercise, body weight) at 6, 12, and 24 months compared to these characteristics at baseline.
2. Clinical events: We will assess if any of the following adverse events are present during the follow-up: angina, myocardial infarction, stroke, hypotensive crisis and death.
3. Use of health services for hypertension at 6, 12 and 24 months.
4. Incremental cost per quality-adjusted life year gained in the intervention group compared to the control group.
5. Views and experiences of patients and health professionals on the self-management (SMBP plus self-titration) of hypertension.

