| Between-group difference in Proportion of days covered with medication (PDC)                                                                                  | Secondary adherence (PDC and persistence) will be estimated using the prescription and dispensing data obtained from the Department's databases and the definitions detailed in section 6.1 will be applied.                                                                                                                                                                  |
| Difference Between Groups in Persistence                                                                                                                      |                                                                                                                                                                                                                                                                                                                                                                               |
| Difference between groups with respect to Therapeutic Inertia (IT)                                                                                            | Quotient between the number of patients whose pharmacological treatment has not been changed divided by the number of patients with SBP and/or SBP measurements taken in consultation at 6, 12, and 24 months of follow-up above the values target according to the recommendations of the European Society of Hypertension and European Society of Cardiology  . |
| Other outcome measures (tertiary endpoints):                                                                                                           |                                                                                                                                                                                                                                                                                                                                                                               |

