#### **11.2 Statistical analysis**

Analysis will be on an intention-to-treat basis for complete cases. We will use mixed models (general linear modeling –GLM) to compare SBP at 12 months between the intervention and control groups. This analysis will be presented in both crude and adjusted forms for the different covariates of interest (baseline BP, gender, GP/PCC-random effect, diabetes, etc.). A sensitivity analysis will be performed to examine the potential effect of missing data, which will include substitution by multiple imputation, replacement of data lost by the most recent data or by the mean of the series. Additionally, analyses of the main outcome measure by subgroups of age, gender, comorbidity, level of chronicity, better control at baseline, etc. will be performed.

Differences in secondary outcome measures (DBP, percentage of patients controlled, PDC, persistence and TI) will be analyzed using methods similar to those used for analysis of the main outcome measure.

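### Therapeutic inertia counts unchanged treatment in all patients over only those off target, so the quotient can exceed 1 and mixes blood pressure control with inertia

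*Protocol*

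**What the plan says.** Section 6.1.2, item 7, makes therapeutic inertia a secondary outcome, "defined as the number of patients whose pharmacological treatment had not been modified, divided by the number of patients not reaching the target values". Target status is judged on "SBP and/or DBP measurements taken at 6 and 12 months of follow-up".

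Table 4 (section 9.1) gives the same measure as "Quotient between the number of patients whose pharmacological treatment has not been changed divided by the number of patients with SBP and/or SBP measurements", and continues with "measurements taken in consultation at 6, 12, and 24 months of follow-up above the values target". It labels the outcome "Difference between groups with respect to Therapeutic Inertia (IT"), so the arms are to be compared on it.

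The two places agree on the form of the quotient: neither restricts the numerator to patients above target. They differ on the visits, because Table 4 adds 24 months. Table 4 also names systolic pressure twice where 6.1.2 names systolic and diastolic.

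Blood pressure control is an outcome in its own right (6.1.2, item 3): "Percentage of patients with SBP <140 mmHg and DBP <90 mmHg at 6, 12 and 24 months of follow-up". For the analysis, section 11.2 lists therapeutic inertia with other secondary outcomes that "will be analyzed using methods similar to those used for analysis of the main outcome measure". Section 7.4 sets an intention-to-treat approach in which all patients are analysed by randomised arm.

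**The concern.** Inertia is meant to describe patients who are above target and whose treatment nevertheless stays the same. As defined, the numerator also takes in patients who have reached target with unchanged treatment, while the denominator leaves them out. Three things follow.

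- The measure is not a proportion and has no upper bound of 1.
- It rises with the share of patients controlled, even if nothing changes in how off-target patients are managed.
- Because the numerator is not a subset of the denominator, no patient has a value of the outcome that could be modelled.

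A separate issue remains even if the numerator is restricted. Who is off target at 6 or 12 months is decided after randomisation, and the intervention aims to change it. The arms are then compared in groups that randomisation did not form.

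What is at stake is how one of seven secondary outcomes reads. An arm with better control and less inertia among its off-target patients could be reported as having more inertia.

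**Working it through.** **Inputs.** The protocol gives no figure for therapeutic inertia, no expected control rates and no rates of treatment change, so there is nothing of its own to reproduce. All rates below are assumptions. The group size of 191 per arm is half of the 382 evaluable patients in section 11.1.

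**1. The quotient as written.** Let c be the share at target, u_on the share with unchanged treatment among those at target, and u_off the same share among those off target. Then

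TI = [c·u_on + (1 − c)·u_off] / (1 − c) = u_off + u_on·c/(1 − c).

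It exceeds 1 when c/(1 − c) > (1 − u_off)/u_on.

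| Assumed u_on, u_off | TI at 20% control | at 50% | at 80% | TI passes 1 at |
|---|---|---|---|---|
| 0.8, 0.5 | 0.70 | 1.30 | 3.70 | 0.625/1.625 = 38% |
| 0.9, 0.3 | 0.53 | 1.20 | 3.90 | 0.778/1.778 = 44% |
| 0.6, 0.6 | 0.75 | 1.20 | 3.00 | 0.667/1.667 = 40% |

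In each row inertia among off-target patients is constant. The rise comes only from better control.

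**2. Two arms, 191 patients each.** Assume 45% (control) and 60% (intervention) at target, 50% and 40% unchanged among those off target, and 85% unchanged among those at target in both arms.

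- Control: off target 0.55 × 191 = 105.05; unchanged 0.50 × 105.05 + 0.85 × 85.95 = 125.6; TI = 125.6/105.05 = 1.20.
- Intervention: off target 0.40 × 191 = 76.4; unchanged 0.40 × 76.4 + 0.85 × 114.6 = 128.0; TI = 128.0/76.4 = 1.68.

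With the numerator restricted to off-target patients, the same inputs give 0.50 and 0.40. Per randomised patient, being both off target and unchanged has frequency 0.50 × 0.55 = 27.5% and 0.40 × 0.40 = 16.0%.

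**3. How far the reversal depends on the 85%.** Let the at-target unchanged share in the intervention arm be u. Its TI is 0.40 + 1.5u, against 1.195 in control. The two are equal at u = (1.195 − 0.40)/1.5 = 0.53. At u = 0.50 the intervention value is 1.15, and the reversal is gone.

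The threshold also moves with the control arm's own share v: 0.40 + 1.5u > 0.50 + (0.45/0.55)v gives u > 0.067 + 0.545v. That is 0.53 at v = 0.85 and 0.39 at v = 0.60.

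**4. The denominator after the numerator is restricted.** Take two patient types in equal numbers, with inertia 0.3 and 0.6 when off target.

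- Control arm, 40% of each type controlled: off-target shares 0.30 and 0.30; TI = (0.09 + 0.18)/0.60 = 0.45.
- Intervention arm, 80% of the first type and 40% of the second controlled: off-target shares 0.10 and 0.30; TI = (0.03 + 0.18)/0.40 = 0.525.

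Inertia within each type is identical in the two arms, yet the restricted ratio differs because the off-target groups differ. Over all patients the numerators alone give 0.27 and 0.21. That difference is due entirely to control.

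**The case against.** **The wording may only be loose.** The name of the measure and its denominator suggest that the numerator was meant to be a subset, and the text is a translation with visible slips. On that reading the quotient is bounded and, with the inputs above, points the right way (0.50 against 0.40). This is fair as a guess at intent. But both definitions omit the restriction, and a prespecified outcome should not rest on a guess.

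**The intervention need not look worse.** A reader might infer that better control always raises the intervention arm's quotient. The documents do not support that. Patients enter with uncontrolled pressure (section 7.1), and the intervention works partly through self-adjustment of drugs (section 6.4.1). Intervention patients at target may therefore often have had a change, which lowers u and can cancel the rise. This part of the objection stands, and the reversal is conditional.

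**The model is not fixed as linear.** A reader might also infer that section 11.2 forces a linear model on a binary outcome. It asks only for similar methods, and its list includes the percentage controlled, which is binary too. The choice of link can be left to the analysis plan. What stands is narrower: as written, the measure has no patient-level value under any model.

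**Off-target selection belongs to the concept.** Inertia can only be observed where the target is missed, so a ratio among off-target patients is the conventional form. The alternative over all randomised patients equals (1 − c)·u_off, so it falls with better control alone and partly duplicates secondary outcome 3. This stands as well: there is no ground for replacing the conventional ratio or reducing it to a descriptive role. It should be labelled for what it is.

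**Conclusion.** The definition is wrong as stated in both places. It counts patients at target with unchanged treatment as inertia, can exceed 1 (from about 38% to 44% control in the three assumed cases), and combines two effects that the trial measures separately. These results follow from the wording and hold whatever the rates turn out to be.

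The direction of any distortion between arms is not determined by the documents. With the assumed rates, the more effective arm looks worse (1.68 against 1.20) if 85% of its at-target patients are unchanged. It no longer does so once that share falls below about 53%.

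The post-randomisation denominator is a real limitation under either reading. It calls for a statement and a companion measure, not for abandoning the ratio. The mismatches in visits and in the pressures named are plain inconsistencies.

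The point is worth correcting, but its reach is limited to this one secondary outcome. The primary outcome and the sample size are untouched.

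**What to change.** 1. In 6.1.2 item 7 and Table 4, define therapeutic inertia at a visit as the number of patients off target at that visit whose antihypertensive treatment was not modified, divided by the number off target at that visit. Each off-target patient then has a value of 0 or 1.
2. Use one set of visits in both places (6 and 12 months, or 6, 12 and 24), and make Table 4 name systolic and diastolic pressure as 6.1.2 does.
3. State that the off-target group forms after randomisation and is affected by the intervention, so the between-arm comparison of this ratio is not a randomised one.
4. Report beside it the proportion of all randomised patients with the visit who are both off target and unchanged. Label it as a supportive measure that also reflects blood pressure control.

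The cost is a few sentences in 6.1.2, Table 4 and 11.2. Table 2 already collects blood pressure and antihypertensive treatments at baseline and at 6, 12 and 24 months, so no new data are needed.

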#### **6.5 Patients follow-up**

The follow-up of the patients will be conducted by the MEFIs in line with routine clinical practice conditions. MEFIs will be responsible for patient selection and inclusion in the trial and will execute the training actions as outlined in point 6.4.

Additionally, the MIC team will reinforce the training and information actions specified by the MEFI and defined in point 6.4. However, it's important to note that the MIC team will not make clinical decisions or modify the management or recommendations of the MEFI. They will also handle data collection during the scheduled visits in the study, including the baseline visit and follow-up visits at 6 and 12 months, working in collaboration with the MEFI.

In the first 12 months of the study, the MIC team will conduct bi-monthly telephone reinforcement sessions. These sessions aim to contact patients in the intervention group with the goal of improving adherence to the intervention and addressing any potential concerns.

In the second year (passive or pragmatic follow-up), patient follow-up will be aligned as closely as possible with routine management in usual clinical practice. Therefore, the role of the MIC will be carried out by a nurse

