### **8.3 Acquisition, packaging and traceability of the medication used in the trial.**

As outlined in section 8.1, all medications, including antihypertensives and other therapeutic groups, will be prescribed in accordance with the criteria of the patient's family doctor, following routine clinical practice. No special conditioning or traceability will be conducted.

Patients will obtain their medications directly from pharmacies with the appropriate official medical prescription.

Nevertheless, the trial drugs' traceability is ensured through electronic prescription and dispensing systems. This technology will allow us to track both the prescriptions issued and the dispensing of medications at pharmacies throughout the trial's duration.

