#### 8.5.5 Treatment visit

Visits to modify treatment, if applicable, will be carried out in the usual context of clinical practice by the patient's family doctor (MEFI) in both the control and intervention groups.

Additionally, the patients of the Intervention group will make visits or telephone consultations to their MEFI when so indicated according to the mode of action according to blood pressure figures, in the event that they must proceed to self-adjust the medication according to the plan. self-adjustment established by the MEFI and registered in the patient's notebook.

In the event that a patient from the intervention group, and based on their objective figures and the instructions received, has to proceed to the self-adjustment at home, they will again follow the mandatory instructions and that are also included in the Patient's Notebook and You will request an appointment with your MEFI within a maximum period of three weeks. On said visit after self-adjustment, the MEFI will review the patient's condition and renew the self-adjustment plan, recording said new self-adjustment plan in the Patient's Notebook.

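### Therapeutic inertia counts any change of drug treatment as action, whatever its direction, and does not tie the change to the above-target reading

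*Protocol*

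**What the plan says.** Section 6.1.2, item 7, has therapeutic inertia "defined as the number of patients whose pharmacological treatment had not been modified, divided by the number of patients not reaching the target values", the target being judged on "SBP and/or DBP measurements taken at 6 and 12 months of follow-up". Table 4 in section 9.1 restates it: "Quotient between the number of patients whose pharmacological treatment has not been changed divided by the number of patients with SBP and/or SBP measurements" that were "taken in consultation at 6, 12, and 24 months of follow-up above the values target". Section 11.2 lists inertia among the secondary outcomes whose differences will be analysed with methods similar to those for the primary outcome.

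Three other places bear on the point.

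- **Where treatment changes.** Section 8.5.5 says "Visits to modify treatment, if applicable, will be carried out in the usual context of clinical practice" by the family doctor in both arms. Intervention patients may also adjust at home under their plan. Section 6.5 says of the collaborating physicians who handle visit data that "the MIC team will not make clinical decisions or modify the management or recommendations of the MEFI".
- **What is recorded at visits.** Table 2 (section 6.6) lists blood pressure and antihypertensive treatments at baseline and at 6, 12 and 24 months.
- **What is recorded between visits.** Section 8.3 says "the trial drugs' traceability is ensured through electronic prescription and dispensing systems", for prescriptions and dispensing alike, over the whole trial.

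**The concern.** Inertia means leaving treatment as it is when blood pressure is above target and a step up would be expected. The opposite of inertia is intensification, not change of any kind. Both definitions use a word for change with no direction attached, so stopping a drug or lowering a dose removes an uncontrolled patient from the inert group. Such changes are foreseeable here: section 6.1.2 lists hypotensive crises among the events to be collected, and the reporting form in Annex 1 has boxes for withdrawal, temporary interruption and dose decrease.

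Both definitions also speak of pharmacological treatment in general, whereas Table 2 uses the narrower antihypertensive treatments. Read to the letter, a change to an unrelated drug would count as action.

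The comparison between arms is at stake. The intervention works by changing how and when medication is adjusted, so both the number and the mix of changes may differ by arm. An outcome that cannot tell a step up from a step down could show a difference, or hide one, for reasons other than how uncontrolled pressure was met.

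**Working it through.** The protocol states no expected rate for this outcome, so there is no figure to reproduce. The check compares the two definitions and then works an illustration with assumed values.

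**The two definitions side by side**

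| Element | Section 6.1.2, item 7 | Table 4 |
|---|---|---|
| Event counted as action | any modification | any change |
| Direction | not stated | not stated |
| Drug class | pharmacological treatment | pharmacological treatment |
| Window relative to the reading | not stated | not stated |
| Time points | 6 and 12 months | 6, 12 and 24 months |

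The rule is thus stated twice, each time without direction. The time points differ between the two places.

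**Effect of ignoring direction**

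Take the numerator as confined to patients above target, which the quotient needs if it is to be a proportion, although neither place says so expressly. Let u be the share of above-target patients with no change at all, which is inertia as worded. Let d be the share of the changed patients who had no intensification. Inertia counted on intensification only is

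TI = u + (1 − u) × d.

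Since (1 − u) × d cannot be negative, the worded rule can only equal or understate this. With u = 0.40 (assumed):

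- d = 0: 0.40 + 0.60 × 0 = 0.40
- d = 0.10: 0.40 + 0.60 × 0.10 = 0.46
- d = 0.20: 0.40 + 0.60 × 0.20 = 0.52
- d = 0.30: 0.40 + 0.60 × 0.30 = 0.58

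**Effect on the comparison between arms**

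- If d is the same in both arms, the difference on intensification is (u₁ − u₂) × (1 − d). For d of 0.10 to 0.30 this is 0.90 to 0.70 of the difference as worded, so the worded rule overstates the contrast.
- If d differs, a real contrast can vanish. With u = 0.40 in both arms and d = 0.10 in one and 0.30 in the other (assumed), the worded rule shows 0.40 − 0.40 = 0, while intensification gives 0.58 − 0.46 = 0.12.

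These figures show the mechanism. They do not forecast what the trial will find.

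**The case against.** The strongest reply is that a protocol may leave operational detail to the statistical analysis plan, which is not shown. For the window this stands: the protocol fixes none, and a later plan may set one. For direction it does not. The protocol does not defer the criterion but states it in two places. Counting only intensification would replace that criterion, not fill it in.

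A second reply is that the drug-class point is literal-minded, since the measure concerns blood pressure targets and Table 2 collects antihypertensive treatments. That is fair as to intent. One added word would settle it.

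A third is that this is the last of seven secondary outcomes and does not touch the primary result. That is correct and limits the weight of the point.

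A reader might also go further and infer that only changes made before the reading can count, so that the outcome misses the response to it. The past tense in section 6.1.2, the recording of pressure and treatment at the same visit, and the restriction on the collaborating physicians all suggest this. The documents do not support it as a statement of fact:

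- Neither definition gives an order of events.
- Section 8.3 makes later changes observable.
- Sections 6.5 and 6.6 have the family physicians, who hold the clinical decisions, collaborating in the visits.
- Under section 7.1 every patient enters with raised pressure, so any change between baseline and month 6 already follows an uncontrolled reading. A patient still above target at month 6 with nothing changed since then is a coherent case of inertia.

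**Conclusion.** The point holds for direction and drug class. As stated, the outcome scores an above-target patient as not inert after a stop, a reduction or, to the letter, a change to an unrelated drug. Inertia is therefore understated, and the contrast between arms can be distorted either way. On assumed values, 0.40 becomes 0.46 to 0.58 when 10% to 30% of changed patients had no intensification. The direction of the error in the level follows from the wording, given a numerator confined to above-target patients. The size rests wholly on the assumed shares, for which the protocol offers no data.

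The link between change and reading is unspecified, so two analysts could score the same patient differently. That is a gap to close. It does not show that the wrong window was chosen, and no size can be given for it. The primary outcome and the sample size are unaffected.

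**What to change.** Amend section 6.1.2, item 7, and the matching row of Table 4 to one common definition:

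- At each time point, among patients above target, take the share with no intensification of antihypertensive treatment, meaning a drug added or a dose increased. Reductions, stops and changes to other drugs do not count as action.
- State one window relative to the reading and apply it identically in both arms, using the prescription and dispensing records of section 8.3.
- State how home self-adjustments are counted.
- Use the same time points in both places, and correct the row's repeated mention of systolic pressure where section 6.1.2 has systolic and diastolic.

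The cost is a few sentences and a date-based extraction from records already tracked, assuming these hold drug and dose.

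There are small downsides. The window is a convention. Home self-adjustments may be incompletely dated: the Notebook contents in section 8.5.1 include the adjustment plan, pressure sheets and contact sheets, but no dated log of adjustments, and the control Notebook has no counterpart. The physician visit that section 8.5.5 asks for within three weeks of a self-adjustment could give an approximate date. If 24 months is kept and the window runs forward from the reading, data after the last visit would be needed, because section 6.8 ends the trial at that visit.
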